### Qualitative data collection

Qualitative data will be used to assist in the process evaluation of the intervention.

Data will be collected through semistructured interviews with GPs, practice staff and patients from intervention and control practices at the end of the study period. GPs and practice staff will be randomly selected from participating practices (*n* ≈ 15 to 40). Patients can opt in to participate by providing their contact details at the end of the online patient survey.

The intervention will be evaluated from the GP’s perspective:

• Changes in GPs’ attitudes towards antimicrobial prescribing;

• How the intervention is implemented;

• How the intervention is integrated with other practice activities;

• How well GPs understand the intervention;

• Whether elements of the intervention are particularly important or problematic.

The intervention will be evaluated from the patient’s perspective:

• Satisfaction with the GP consultation;

• The process of care;

• Evaluate the intervention components as stated above.

### Qualitative data analysis

Analysis of qualitative data will be completed using NVivo-9 qualitative data analysis software. Data analysis will follow an inductive approach through thematic analysis. A cross-comparison of qualitative analysis will be conducted by two team members, one not directly involved in the interview process; along with active discussion of findings with the wider project team, this will help ensure the rigour of the thematic analysis.

### Economic evaluation

The economic cost of UTIs in primary care consists of direct costs associated with health care utilization and drug costs, indirect costs associated with lost productivity, premature mortality and intangible costs, such as the cost of pain and discomfort to the individual. In addition, increasing resistance to antimicrobials has implications for the economic costs of UTIs. In particular, potential treatment failure as a result of resistance means an increase in the use of more expensive alternative treatments, as well as potential increases in healthcare utilization.

The economic analysis will take a two-staged approach.

1. A within-intervention analysis will be conducted, using the cost per rate of first-line antimicrobial prescribing to assess the costs and effects of the intervention arms in comparison with the control arm.

2. Modelling analysis of the impact of prescribing adherence will be undertaken. This will facilitate the identification, valuation and extrapolation of the wider impact of prescribing adherence.

The costs taken into account will be:

• Intervention costs: direct costs will include intervention costs, capital costs, cost of providing workshops, learning materials, leaflets and any other materials.

• Health services costs include GP consultation time, use of hospital services, additional laboratory service costs and prescription costs.

The cost-effectiveness will be assessed by relating the mean differential cost per practice between the intervention arms and the control, to their differential effectiveness. Incremental cost-effectiveness ratios will be calculated and subjected to sensitivity analysis. The primary outcome will be cost per prescription of first-line antimicrobials.

In addition, it is likely that some of the costs and consequences of the intervention will continue after the intervention period has ended, for which an additional economic evaluation will be performed. This modelling analysis will facilitate the extrapolation of the costs and outcomes over time with data obtained from the within-intervention analysis. Where there are evident gaps in the available data, data will be obtained from the literature following a systematic approach.

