• A professional development programme for the GP, which includes interactive workshops, audit and feedback reports on antimicrobial prescribing and electronic antimicrobial prescribing prompts to improve the quality of prescribing. The quality of prescribing is defined within this study as the prospective prescribing of first-line antimicrobials in accordance with the Guidelines for Antimicrobial Prescribing in Primary Care in Ireland.

• Delayed antimicrobial prescribing for UTIs in one study arm, to decrease the consumption of antimicrobials.

• A supportive framework to inform patients of AMR through multimedia applications within the waiting room of the GP.

• Novel e-health technology, which includes an electronic data extraction system that will remotely collect anonymized data from all consultations with patients diagnosed with a UTI by the GPs and mobile health technology to monitor and record antimicrobial consumption behaviour of patients.

By integrating this intervention into routine care and making all material freely available at the end of the intervention, the SIMPle study strives to be sustainable and self-promoting and, thereby, implemented in primary care in Ireland beyond the intervention period.

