**GP focused**				
Coding workshop	All arms	Demonstrate the purpose of electronically coding UTI consultations using coding guidelines (International Classification of Primary Care code U71) and how to implement uniform coding in routine practice.	Promote routine uniform consultation coding for UTIs.	Gather baseline practice data and knowledge and attitudinal data (questionnaires).
Interactive workshop A	Intervention arm A	Raise the profile of GPs’ antimicrobial prescribing behaviours and their role in the broader issue of AMR.	Encourage GPs to become more aware of their antimicrobial prescribing behaviours through discussion of their role in the development of AMR.	Process evaluation
		Provide guidance on antimicrobial prescribing through adherence to guideline for UTI.		
Interactive workshop B	Intervention arm B	In addition to the core components of interactive workshop A, the recommendation to delay antimicrobial prescribing for UTIs facilitated through shared decision making will be promoted.		Encourage the use of delayed prescribing for UTIs.
				Process evaluation.
Electronic audit and feedback reports	Intervention arms A and B	A monthly report will be available (electronically) to practices summarizing their antimicrobial prescribing patterns for UTIs and antimicrobial resistance patterns of *E. coli*.	To provide a comparison of antimicrobial prescribing for UTIs between practices.	To provide an overview of antimicrobial resistance patterns in *E. coli* causing UTIs.
Stakeholder awareness		Information about the intervention and the issue of AMR will be provided to other stakeholders; pharmacists, practice receptionists and practice nurses.	To update all stakeholders on the overall aim of the intervention.	
Computer “prompt” application	Intervention arm A	Upon entry of the uniform UTI code, automated electronic prompts will appear on the GPs computer screen.	Provide the recommended antimicrobial treatment for a UTIs.	Remind the GP to collect urine samples and patients’ mobile telephone numbers.
	Intervention arm B		Provide the recommended antimicrobial treatment for a UTI and suggest delayed prescribing.	

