#### Primary outcome: adherence to the guidelines for antimicrobial prescribing in primary care in Ireland

Comparison of antimicrobial prescription data will be made between control and intervention arm A.

• Each consultation will be categorized according to whether an antimicrobial was prescribed (yes/no) and if so, whether first-line antimicrobials were prescribed (yes/no).

• Antimicrobial prescribing rates will be determined for each intervention arm per month for first-line, second-line and other antimicrobials as specified in the Guidelines for Antimicrobial Prescribing in Primary Care in Ireland.

• The proportion of antimicrobial prescribing according to first-line treatment for each intervention arm will be calculated by determining the number of first-line prescriptions as a percentage of the total number of antimicrobial prescriptions for UTIs.

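### The economic evaluation measures effect only by first-line prescribing and only against control, so it states no ratio that values what arm B adds to arm A

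*Protocol article*

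**What the plan says.** All of the following is in the protocol article.

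- **Effect measure.** Under Economic evaluation, the within-intervention analysis works by "using the cost per rate of first-line antimicrobial prescribing to assess the costs and effects of the intervention arms in comparison with the control arm". The same section later says: "The primary outcome will be cost per prescription of first-line antimicrobials".
- **Comparator.** Cost-effectiveness is assessed by "relating the mean differential cost per practice between the intervention arms and the control, to their differential effectiveness". No step from arm A to arm B is named.
- **Model.** The second stage concerns adherence: "This will facilitate the identification, valuation and extrapolation of the wider impact of prescribing adherence".
- **Costs.** "Health services costs include GP consultation time, use of hospital services, additional laboratory service costs and prescription costs". Intervention costs are counted as well.
- **What arm B adds.** Intervention development overview gives its purpose: "Delayed antimicrobial prescribing for UTIs in one study arm, to decrease the consumption of antimicrobials". Table 1 describes workshop B as the core of workshop A plus the promotion of delayed prescribing by shared decision. The prompt gives both arms the first-line recommendation, and in arm B it also suggests delayed prescribing.
- **Clinical definition.** Under Quantitative data analysis, the primary outcome is a share, obtained by "determining the number of first-line prescriptions as a percentage of the total number of antimicrobial prescriptions for UTIs".
- **Consumption.** It is a secondary objective, has its own sample size paragraph, and is to be compared between arms A and B from text-message replies.

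**The concern.** Control, A and B are three alternative packages. Whether to add delayed prescribing to A depends on the step from A to B: what it costs and what it gains. The economic section uses an effect measure that the added component is not aimed at, and a comparator that leaves that step out. Followed as written, it produces two ratios against control, both on the first-line scale. Neither says whether delayed prescribing is worth its cost.

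The measure is also described in two ways, per rate and per prescription. On a share, a fall in total prescribing is neutral. On a count, it lowers the effect credited to the arm that achieves it.

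The economic objective is at stake, and with it the statement under Anticipated outcomes that the study will inform the uptake of individual parts of the intervention as well as the whole.

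**Working it through.** The article gives no cost, cost-effectiveness ratio or threshold, so there is no stated figure to reproduce. The check has three parts.

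**1. When is B dominated by A?** Let C be cost and E the economic effect. B is dominated when C_B ≥ C_A and E_B ≤ E_A, with at least one inequality strict. On the share scale, with control at 38% and A at 48% (the Sample size section's absolute 10% increase):

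- B at 48%: E_A = E_B = 10 points. If B costs more, it is dominated, however far consumption falls.
- B at 53% (assumed): E_B = 15 points against 10. B is not dominated at any cost.
- B at 46% (assumed): E_B = 8 points against 10. B is dominated if it costs at least as much as A.

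The reduction in consumption appears in none of these effects. It can act only through C_B.

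**2. What if the effect is a count?** Inputs per 1,000 UTI patients, from Sample size: 56% receive an antimicrobial and 38% of prescriptions are first-line. The paragraph on decreased consumption gives a 20% fall through delayed prescribing and does not say whether this is relative or absolute. Two assumptions are needed: B has A's 48% share, and the fall carries over to prescriptions issued.

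| Arm | Prescriptions | First-line | Change v control |
|---|---|---|---|
| Control | 1,000 × 0.56 = 560 | 560 × 0.38 = 212.8 | – |
| A | 560 | 560 × 0.48 = 268.8 | +56.0 |
| B, 20% relative fall | 560 × 0.80 = 448 | 448 × 0.48 = 215.0 | +2.2 |
| B, 20-point fall | 1,000 × 0.36 = 360 | 360 × 0.48 = 172.8 | −40.0 |

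To match A's count, B would need a first-line share of 268.8 / 448 = 60.0% or 268.8 / 360 = 74.7%. If delayed prescriptions are issued and recorded as usual, the count falls less. With no fall in prescriptions issued, B at 48% gains the same 56 as A.

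**3. How much effect is left out?** The planned fall in consumption is 560 − 448 = 112 per 1,000 (relative) or 560 − 360 = 200 per 1,000 (absolute). The article's sample size of 240 fits the absolute reading better. For 56% v 36%, with continuity correction, 107 per arm before clustering, ICC 1% and 10 practices per arm, the total is 2 × 107 × 0.99 / (1 − 107 × 0.01 / 10) = 237. The relative reading (56% v 44.8%) needs about 900 or more. The text itself does not settle it.

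Two limits apply. The figure is for B against control, so it equals the step from A to B only if A leaves consumption unchanged, and A's patients also receive leaflets on antimicrobial use. The 56% is also the proportion prescribed an antimicrobial, not the proportion who took one.

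**The case against.** A reader might infer that B must come out dominated whenever it costs more than A. The article does not support that. Dominance also needs B to be no better on first-line prescribing, and nothing fixes the two arms' shares as equal. B receives A's core content plus shared decision making, so its share could be higher, equal or lower.

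Nor does arm B go wholly unrewarded. Prescription, consultation, hospital and laboratory costs are counted, so fewer prescriptions or reconsultations would lower B's net cost, possibly below A's. That credit is partial. The extracted data record prescribing, while consumption is known only from texts, so a prescription issued but never taken may still be costed. A lower drug bill also does not value reduced antimicrobial exposure, which is the reason for the trial.

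A third objection is that nothing is lost by comparing only with control. For point estimates this is correct: (C_B − C_A) / (E_B − E_A) follows by subtraction from the two comparisons. The uncertainty of that step does not follow from the two separate intervals, because both share the control arm and their covariance is needed. Subtraction also stays on the first-line scale.

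Finally, first-line prescribing is called the primary economic outcome, sensitivity analysis and longer-term modelling are planned, and a condensed article may leave secondary measures to a fuller plan. Using the trial's own primary outcome, which is captured from all coded consultations, is a reasonable choice and should stay. The point concerns what the article does state: an effect measure given twice, an adherence model and a comparator, none of which reaches arm B's added aim.

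**Conclusion.** The point holds in a limited form. The stated economic effect is first-line prescribing and the stated comparator is control. Reduced consumption, the aim of arm B's added component, has no effect-side value, and no B v A increment is named. B is dominated by A if it costs more and does not exceed A on first-line prescribing. The claims that B must rank below A, or that its benefit cannot count at all, are not supported.

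The size depends on how the measure is read. On a share, a fall in prescribing is neutral. On a count, at a 48% share, B's gain per 1,000 UTI patients is about +2 (20% relative fall) or −40 (20-point fall), against +56 for A. This assumes that the planned fall in consumption shows up in prescriptions issued. No cost per course avoided can be given, because the article states no costs. The issue affects a secondary objective and leaves the trial's primary comparison untouched.

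**What to change.** In the Economic evaluation section:

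1. Keep first-line prescribing as the primary economic effect. Define it as the share of UTI antimicrobial prescriptions that are first-line, as in the clinical primary outcome, and use that definition in both places where the measure is named.
2. Add a secondary effect measure, cost per antimicrobial course avoided, based on the text-message consumption data already planned for comparing A with B. Control practices also request mobile numbers, so control could be included where replies allow.
3. Report total antimicrobial prescribing from coded consultations beside it, as a check that does not depend on who replies.
4. Order control, A and B by cost and report fully incremental ratios, including B v A, with dominance and uncertainty stated.
5. Say whether the 20% fall in consumption is relative or absolute.

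This costs a few lines and some further analysis, with no new data collection. The drawback is that the consumption measure rests on text responders, so it must carry the selection caveat that the article already gives under Limitations of the study.

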## Discussion

### Anticipated outcomes

Utilizing a multidisciplinary perspective and social marketing conceptual framework, this study will contribute an understanding of the key behaviours and social norms that motivate change in GPs antimicrobial prescribing and patient antimicrobial consumption behaviours. The intervention will provide an evaluation of the different parts and thereby provide evidence to implement individual or all parts of the intervention beyond the study area and period.

### Anticipated publications

• A qualitative study of the formative research that underpinned the development of the intervention.

• A description of the multidisciplinary intervention to improve quality and quantity of antimicrobial prescribing in primary care (protocol).

• A quantitative analysis of the impact of the intervention on the quality and quantity of antimicrobial prescribing in primary care.

• An economic analysis of the intervention to improve antimicrobial prescribing in primary care including future cost estimates.

• Given the community focus of this research, findings will be disseminated through local print and online media, to include the widest possible audience.

### Limitations of the study

The method of data collection used requires a coding workshop to improve routine consultation coding for UTIs in all practices participating in the intervention, including those in the control group. The inclusion of the control group in the coding workshop may affect the outcome; however antimicrobial treatment was not discussed at these workshops. To limit this bias, researchers delivering the workshops were blinded as to randomization of practices to intervention and control. This bias is anticipated to increase awareness in the control group, resulting in a potentially smaller difference between intervention and control arms.

Computerized remote data extraction will be used to assess differences between the intervention and control arms. Data analysis will not be blinded. However, as the outcome is an absolute comparison in first-line prescriptions of antibiotics, before and after the intervention, the risk of bias is minimal.

The use of patient mobile telephone numbers for evaluation purposes, while novel and direct, introduces selection bias, owing to different levels of mobile phone penetration and familiarization with their use. For research evaluation purposes, however, the implementation of follow-up by mobile telephone technology allows evaluation of consumption (and thereby the impact of delayed prescribing) rather than simply the evaluation of prescribing behaviour by GPs. However, since the sample can be related back to the source population and the selection bias can be estimated, the final evaluation can be considered within this context.

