[50].

Educational videos displayed in the practice waiting room can also increase patients’ understanding and satisfaction of their care, as well as empowering patients to discuss their treatments further with the GP
[51,52]. Previous research examined the effectiveness of a multimedia campaign in comparison with a static educational brochure to improve treatment for chronic illness in practice waiting rooms with patients with low health literacy
[53,54]. This approach was considered novel, effective and acceptable in improving health care management, by empowering patients to discuss making positive changes to their treatment with their GP
[54]. Audiovisual messages played in practice waiting rooms have also proven effective in increasing patient uptake of vaccines
[55].

Mobile phone technology can facilitate rapid and cost-effective access to a study group of interest to facilitate data collection. Previous programmes have successfully used text messages to assess consumption and adherence to antimicrobial treatments with 72% patient participation for follow-up
[56].

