#### Follow-up data

Evaluative information from the patients will be obtained via text message. These text messages will require a minimal response (at no cost) from the patient and will be used to assess actual consumption of the prescribed antimicrobial. Patients can discontinue receiving these text messages at any time by replying STOP.

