### Quantitative data analysis

Data comparisons will be made between the start and end of the intervention. To assess sustainability, an additional comparison will be made six months after the end of the intervention. An overview of the data collected through the iPCRN, as outlined in data collection, will be presented for both practice and patient variables. Data will be presented and compared between each arm. Patients’ characteristics will be compared between the group who were followed up by text messaging and the group who did not participate in text messaging.

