#### Outcome: frequency of antimicrobial prescribing and consumption

The frequency of antimicrobial prescribing will be compared between the control and each intervention arm (arms A and B).

• Consultations will be analyzed according to whether an antimicrobial was prescribed or not (yes/no).

• The prescription rates per group per month for each antimicrobial group will be calculated as the number of antimicrobial prescriptions per 1,000 consultations per month.

• Comparison of the overall reduction over the period of the intervention will be based on the percentage of consultations where an antimicrobial was prescribed at the start of the intervention, as compared with the end.

The frequency of antimicrobial consumption will be compared between intervention arms A and B, according to their response to the text messages.

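### Selection bias in text-message follow-up cannot be estimated as the limitations section claims, because consumption is seen only in patients who reply

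*Protocol article*

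**What the plan says.** Under Limitations of the study, the protocol article accepts that follow-up by mobile phone "introduces selection bias, owing to different levels of mobile phone penetration and familiarization with their use". It then argues that, "since the sample can be related back to the source population and the selection bias can be estimated", the final evaluation can be read in that light.

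The check that belongs to this claim is in Quantitative data analysis: patients' "characteristics will be compared between the group who were followed up by text messaging and the group who did not participate in text messaging". That sentence names two groups and no arms. The sentence just before it says "Data will be presented and compared between each arm".

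Consumption is compared between arms A and B "according to their response to the text messages", and compliance with the 48-hour wait also comes from the texts. Under Informed consent, patients enter text follow-up by replying to a first message. Under Follow-up data, "Patients can discontinue receiving these text messages at any time by replying STOP".

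Two further passages bear on the point. Method of quantitative data analysis plans a multilevel logistic model that adjusts for baseline prescribing and for patient- and practice-level confounders. Consultation data lists what is extracted: prescribing, urine results, consultations, age, sex, medical card status and coded comorbidities. Consumption is not on that list.

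**The concern.** A comparison of recorded characteristics shows how far the participants resemble everyone else on those characteristics. It says nothing directly about consumption in the patients who did not reply, because nobody observes it. To turn the comparison into an estimate of bias, one must assume that non-responders consume as responders with the same recorded characteristics do, and the data cannot test that assumption.

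The limitation names only phone access and familiarity as causes of selection. Entry also depends on the GP asking for the number, a urine form being sent and the patient opting in, and patients can leave at any time. Willingness to answer may depend on whether the patient followed the advice given, and only arm B practices are supported in recommending a 48-hour delay.

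Lowering consumption is the stated purpose of delayed prescribing in arm B, and the outcome has its own sample size. At stake is how much weight a reader may put on the consumption difference. If the limitation stands as written, balanced characteristics could be taken as evidence that the contrast is sound.

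**Working it through.** **1. The benchmark.** The article gives no figure for the selection bias, but it does size the consumption outcome: 240 patients, 20 practices, 80% power, ICC 1%, starting from 56% with a 20% decrease. Reading the decrease as absolute (56% to 36%), two-sided 5% (sidedness assumed), with continuity correction, gives 107 per arm, 214 in total. With N/20 patients per practice, N = 214 × [1 + (N/20 − 1) × 0.01], so N × (1 − 0.107) = 211.86 and N = 237.2, close to 240. A relative decrease (56% to 44.8%) gives 898 without and 975 with the correction. The planned effect is therefore 20 percentage points.

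**2. General formula.** In one arm, let r be the participation rate and g the consumption of non-responders minus that of responders.

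- True consumption = observed + (1 − r) × g.
- With the same r in both arms, the error in the arm difference has size (1 − r) × |g in B − g in the comparator|.

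The only participation figure in the article is "72% patient participation for follow-up", from earlier programmes. Used here as an assumption, r = 0.72 and 1 − r = 0.28. The differences in gap are also assumed:

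| Arm difference in gap | Bias in the contrast |
|---|---|
| 10 points | 0.28 × 10 = 2.8 points |
| 20 points | 0.28 × 20 = 5.6 points |
| 30 points | 0.28 × 30 = 8.4 points |
| 0 | 0 |

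**3. Selection on consumption itself.** Take true consumption p = 56% in both arms, so no effect. The observed value is p × rc / [p × rc + (1 − p) × rn], where rc and rn are the response rates of consumers and non-consumers (assumed, about 72% overall in each arm).

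- Both arms rc = 80%, rn = 62%: 0.448 / 0.7208 = 62.2% in each arm. Levels are biased, the contrast is not.
- Arm A 72/72, arm B 62/85: 56.0% against 0.3472 / 0.7212 = 48.1%, a spurious −7.9 points.
- Arm A 80/62, arm B 72/72: 62.2% against 56.0%, −6.2 points.
- Arm A 80/62, arm B 62/85: 62.2% against 48.1%, −14.0 points.

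**4. Why the arm split matters.** Take a recorded characteristic X present in half the patients of each arm. In arm A, 90% of those with X and 54% of those without respond; in arm B the reverse. Overall response is 72% in each arm. Consumption is 71% with X and 41% without, in both arms.

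- Arms combined: (0.45 + 0.27) / (0.72 + 0.72) = 50% of responders have X, so participants and non-participants look identical.
- By arm: 0.45 / 0.72 = 62.5% in A and 0.27 / 0.72 = 37.5% in B.
- Observed consumption: 0.625 × 71 + 0.375 × 41 = 59.75% in A and 0.375 × 71 + 0.625 × 41 = 52.25% in B, a spurious −7.5 points.

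A by-arm comparison reveals this, and adjustment for X removes it. Neither would reveal or remove the selection in step 3.

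**5. Bounds.** At 72% participation, the true difference lies within 0.72 × observed ± 28 points if nothing is known about non-responders. The texts ask about prescribed antimicrobials, so a linked non-responder with no prescription can be counted as a non-consumer. If 56% of non-responders in each arm were prescribed (assumption), the half-width is 0.28 × 0.56 = 15.7 points, on the all-patient denominator to which the 20-point effect refers.

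**The case against.** Four points can fairly be made for the article.

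- **Arm split.** A reader might infer that the check combines the arms. The text does not say so, and the general statement about comparing data between arms allows a by-arm reading. What stands is only that the check does not state it.
- **Adjustment.** A reader might also infer that nothing corrects the consumption result. The multilevel model adjusts for patient- and practice-level variables, which covers recorded factors of the kind the check would show to be unbalanced. It does not reach selection on consumption or on unrecorded factors. Weighting responders by their response probability rests on much the same assumption and has the same limit.
- **Disclosure.** The limitation openly names selection bias and claims no correction. That is true, but it does say that the bias can be estimated, and that is the part that fails.
- **Missing-data methods.** An article commonly leaves these to the full protocol or analysis plan. Their absence is not the point; the assertion is.

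The strongest reading, that the consumption contrast is biased, is not supported. No passage shows different selection in arms A and B, and both arms have the same prompt to collect phone numbers. For control against B, the contrast used in the sample size, the reminder prompt is described for the intervention arms only, so selection could more easily differ. The article should reconcile which of the two contrasts it intends.

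**Conclusion.** The claim that the selection bias can be estimated goes further than the described methods support. The check and the model can describe selection on recorded factors and partly remove it. Selection tied to unseen consumption or to unrecorded factors cannot be estimated, and it harms the contrast to the extent that it differs by arm.

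The size cannot be known from the article. The illustrations give 2.8 to 8.4 points from the gap formula and about 6 to 14 points from the response-rate scenarios, against 20 planned. They rest on 72% participation borrowed from earlier programmes and on gaps and response rates that I assumed. A reader might take ±28 points as the uncertainty to set against the 20-point effect. On the all-patient denominator, with linked prescribing records and 56% prescribed, it is nearer ±16.

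The outcome is secondary and the primary prescribing outcome is unaffected. Frequency of delayed prescribing and reconsultation also inform on delayed prescribing, and neither is described as resting on the texts. The correction is still worth making, because it changes what the consumption result can support.

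**What to change.** - **Limitations of the study:** replace the claim with a statement that differences in recorded characteristics can be described and adjusted for, while selection on unobserved consumption cannot be estimated.
- **Quantitative data analysis:** report participation by arm, and compare participants with non-participants within each arm.
- **Consumption outcome:** add a best/worst-case or tipping-point range for unseen consumption, counting patients with no recorded prescription as non-consumers where the records can be linked. Inverse-probability weighting on the extracted variables is optional.

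This needs no new data collection. It costs a little extra analysis and a less favourable limitation statement.
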